### Study population

A total of approximately 2,340 adults will be enrolled from five participating centers, representing Han, Hui, Tibetan, and Kazakh populations across regions with varying altitude, environmental exposure, and healthcare accessibility. Recruitment targets are prespecified according to catchment characteristics, with planned enrolment of 900–1,050 Han, 650–750 Hui, 400–500 Tibetan, and 250–350 Kazakh participants. Sample size estimation is based on an event-driven approach (Supplementary Material 1). Assuming a 4% cumulative incidence of first AMI over 24 months, approximately 80 events are expected, supporting multivariable modeling and subgroup analyses.

Participants will be eligible if they: (1) are aged 30–85 years; (2) have an estimated 10-year atherosclerotic cardiovascular disease (ASCVD) risk ≥20% (6); (3) are permanent residents of the study area (≥6 months per year); (4) provide written informed consent; and (5) agree to repeated follow-up and biospecimen collection. Exclusion criteria include: (1) major comorbid conditions such as end-stage renal disease, hepatic failure, or active malignancy; (2) acute illness at enrolment; (3) severe psychiatric disorders; (4) substance abuse; and (5) pregnancy or breastfeeding (17). Loss to follow-up is defined as absence from more than two scheduled visits or permanent discontinuation. Follow-up will be maintained through clinic visits supplemented by telephone or electronic contact where necessary.

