Baseline assessment: The project will be carried out from 2025 to 2027 in Gansu Provincial People’s Hospital, Aksay County People’s Hospital, Linxia Prefecture People’s Hospital, Gannan Tibetan Autonomous Prefecture People’s Hospital, and Dingxi City People’s Hospital. High-risk cardiovascular patients of the Han, Hui, Tibetan, and Kazakh ethnic groups will be identified through cardiovascular outpatient clinics, community screening programs, and electronic medical record systems. Follow-Up: it will be conducted at 3, 6, 9, 12, 15, 18, 21, and 24 months after enrollment in the cohort, for a period of 2 years. *Standardized assessment: Demographics, lifestyle, psychology, diet, and medication adherence questionnaires. +Sociodemographic characteristics: Age, sex, ethnicity, residence type, education, occupation, and income. ++Lifestyle factors: Smoking, alcohol consumption, dietary habits, physical activity, and sleep quality. †Clinical history: Hypertension, diabetes, dyslipidemia, previous stroke or TIA, family history of coronary heart disease, and history of drug use. ‡Anthropometry and physiological parameters: Including height, weight, BMI, waist circumference, blood pressure and body fat percentage. **Fasting venous blood tests: High-sensitivity C-reactive protein (hs-CRP), high-sensitivity troponin I (hs-TnI), creatine kinase (CK), creatine kinase-MB (CK-MB), lactate dehydrogenase (LDH), aspartate aminotransferase (AST), soluble suppression of tumorigenicity 2 (sST2), N-terminal pro–B-type natriuretic peptide (NT-proBNP), lipoprotein-associated phospholipase A2 (Lp-PLA2), fasting glucose, insulin, hemoglobin A1c (HbA1c), and a full lipid panel (total cholesterol, low-density lipoprotein cholesterol(LDL-C), high-density lipoprotein cholesterol (HDL-C), and triglycerides. ¶72-h wearable electrocardiogram (ECG) monitoring: A validated clinical-grade device (Shanghai Yishi Technology Co., Ltd.) will be used to continuously conduct 72-h wearable ECG and heart rate variability (HRV) monitoring. The data will be transmitted in real-time to a secure cloud platform, and the NARON CardioAI system will be used for automatic analysis, waveform classification, and feature extractio. ¶¶Transthoracic echocardiography: Unless there are other clinical indications, an echocardiogram will be performed once a year to evaluate the left ventricular ejection fraction and the situation of abnormal wall motion. ***Coronary computed tomography angiography (CCTA): If there are clinical indications should be repeated every 12 months. Assessment Tools: Includes the Rose Angina Questionnaire, The Canadian Cardiovascular Society Angina Classification, The Patient Health Questionnaire-9 (PHQ-9), The Generalized Anxiety Disorder-7 (GAD-7), The Perceived Stress Scale - 10 (PSS-10), The Pittsburgh Sleep Quality Index (PSQI), The Semi-quantitative Food Frequency Questionnaire (FFQ), The International Physical Activity Questionnaire Short Form (IPAQ-SF), The General Medication Adherence Scale (GMAS).

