#### Follow-up assessments

Participants are followed every 3 months over 24 months using a standardized schedule (Table 1). This repeated-measures design allows assessment of temporal changes in risk indicators and their potential association with short-term cardiovascular events. At each visit, symptom status, interim medical events, medication use, and health-related behaviors are updated. Biomarkers are measured at regular intervals, and ECG monitoring is repeated every 6 months. Echocardiography is repeated annually, and CCTA is performed when clinically indicated. All suspected AMI events are adjudicated by an independent, blinded cardiology panel according to the Fourth Universal Definition of Myocardial Infarction (2018) (21).

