#### Nested case–control component

Within the cohort, participants who develop incident AMI will be defined as cases, and matched controls will be selected from the risk set. Stored biospecimens from these participants will be used to assess variation in circulating biomarkers as short-term risk indicators prior to AMI, supporting analysis of temporal changes in risk within the cohort.

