#### Primary outcome analysis

Associations between baseline variables and time to first incident AMI will be evaluated using Cox proportional hazards regression models. Follow-up time will be calculated from enrolment to AMI, loss to follow-up, death, or end of study. Multivariable models will include prespecified variables, including age, sex, ethnicity, smoking status, systolic blood pressure, diabetes status, lipid profile, and environmental exposures. Additional variables will be selected based on clinical relevance. Continuous variables will be modeled on their original scale, and nonlinearity will be assessed using restricted cubic splines. Hazard ratios (HRs) and 95% confidence intervals (CIs) will be reported. The proportional hazards assumption will be assessed using Schoenfeld residuals.

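### Loss to follow-up ends time at risk but has no date, and its missed-visit count acts late or not at all, so 3, 6 or 9 months without a visit can be counted as AMI-free

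*Protocol article*

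**What the plan says.** The Protocol article, Study population, defines loss in two alternative parts: "Loss to follow-up is defined as absence from more than two scheduled visits or permanent discontinuation". The next sentence adds: "Follow-up will be maintained through clinic visits supplemented by telephone or electronic contact where necessary".

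Primary outcome analysis then makes loss one of the events that close the time at risk in the Cox model: "Follow-up time will be calculated from enrolment to AMI, loss to follow-up, death, or end of study".

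The notes to Table 1 give the visit schedule: "it will be conducted at 3, 6, 9, 12, 15, 18, 21, and 24 months after enrollment in the cohort". Follow-up assessments says that interim medical events are updated at each visit. In the nested case–control component, "matched controls will be selected from the risk set".

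The article does not say on which date a loss is placed (last visit, last contact, or the day the definition is met). It does not say how permanent discontinuation is established for someone who simply stops coming, or whether the missed visits must be consecutive.

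**The concern.** A missed-visit count is a reasonable way to report retention. Here it also acts as a censoring event, and the two uses do not fit together. A censoring time should be the last moment at which the participant was known to be free of AMI. A count of more than two missed visits is reached well after that moment, or not before month 24 at all.

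Time in which nobody knew the participant's AMI status would then sit in the denominator as event-free time and lower the estimated AMI rate. If attendance differs by healthcare access or ethnicity, the amount of such time differs by the very factors the study compares. The same participants would stay in the risk set from which nested controls are drawn, although their AMI status at the case's index date is unknown.

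**Working it through.** **Inputs.** Follow-up visits at months 3, 6, 9, 12, 15, 18, 21 and 24 (notes to Table 1); loss by count requires at least three missed visits (Study population); about 2,340 participants, 4% incidence over 24 months and about 80 events (Study population). No dropout rate is stated in the article.

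**The plan's own figure.** 2,340 × 0.04 = 93.6 events, not 80. Working back, 80 / 0.04 = 2,000 and 1 − 2,000/2,340 = 14.5%. The stated 80 is therefore consistent with an allowance of about 15% loss, but the article does not state one; the calculation is in Supplementary Material 1, which is not shown. I use 14.5% only to set a scale. It treats lost participants as contributing nothing, whereas below they contribute observed time up to their last visit.

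**Step 1: when the count is met.** Take a participant who attends every visit up to month L and none afterwards. (If scattered misses are added together, someone with earlier missed visits reaches the count sooner.)

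| Last attended visit | Visits missed | Third missed visit | Months without a visit before time ends |
|---|---|---|---|
| 0, 3, 6, 9, 12, 15 | 8, 7, 6, 5, 4, 3 | 9, 12, 15, 18, 21, 24 | 9 in each case |
| 18 | 2 | never | 6 (to month 24) |
| 21 | 1 | never | 3 (to month 24) |

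The last column assumes that loss is dated when the count is met, and that those who never meet the count run to the end of study.

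**Step 2: mean credited time per dropout.** Assume last visits are spread evenly over the eight values 0 to 21 (mean 10.5 months) and that nothing is learned in the gap.

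- Loss dated at the third missed visit: (6 × 9 + 6 + 3)/8 = 63/8 = 7.875 months.
- Loss dated back to the last contact, with only the month 18 and 21 group running on: (6 + 3)/8 = 1.125 months.
- Permanent discontinuation also applied to the month 18 and 21 group, and every loss dated at last contact: 0 months.

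**Step 3: share of person-time.** With dropout f and mean credited time c, share = f·c / [(1 − f)·24 + f·(10.5 + c)].

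- f = 14.5%, c = 7.875: 1.142/23.184 = 4.9%; 2,340 × 0.145 × 7.875/12 = 223 person-years.
- f = 14.5%, c = 1.125: 0.163/22.206 = 0.7%; 2,340 × 0.145 × 1.125/12 = 32 person-years.

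| Assumed dropout | Loss at third missed visit | Only month 18 and 21 group |
|---|---|---|
| 5% | 1.7% | 0.2% |
| 10% | 3.4% | 0.5% |
| 14.5% | 4.9% | 0.7% |
| 20% | 6.9% | 1.0% |
| 30% | 10.6% | 1.7% |

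Under a constant hazard, the AMI rate is understated by the same share.

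**Step 4: what a difference between centres could do.** This is purely illustrative, since the article gives no attendance by centre. Take equal true risk and dropout of 5% against 30%. The false rate ratio is (1 − 0.106)/(1 − 0.017) = 0.91 on the larger reading and (1 − 0.017)/(1 − 0.002) = 0.99 on the smaller.

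**The case against.** Several points on the other side stand.

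- A reader might infer that someone who vanishes after month 18 or 21 can never be classed as lost. The documents do not support that: the same sentence offers permanent discontinuation as an alternative route. Only the missed-visit count is out of reach.
- A reader might also infer that the plan prescribes counting the gap as AMI-free. It does not. Study population says who is lost; no section says when that person's time ends. If losses are dated at last contact, the participants last seen at months 0 to 15 drop out of the sum, and they supply 54 of the 63 months in Step 2.
- A missed visit is not the same as unknown AMI status. Telephone or electronic contact is provided for, and interim events are collected from participants who return. Either makes part of the gap observed.
- The dropout rate, its even spread and the contrast between centres are assumptions. Even a ratio of 0.91 is small against the study's precision: with 80 events split 40/40, SE(log ratio) = √(1/40 + 1/40) = 0.22, while log 0.91 = −0.09, about 0.4 SE.
- The harm to the nested controls is small. A 4% risk over 24 months is a hazard of about 0.0017 per month. Even 223 person-years then hold only 223 × 12 × 0.0017 ≈ 4.5 AMIs, about 0.2% of 2,340 participants.

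The remaining objection is that a journal article may leave censoring dates to a full protocol or analysis plan. This does not dispose of the point. The article states both the threshold and its use to end follow-up, and applying the two literally gives the table in Step 1. A fuller document may supply a date, but the stated rule is a poor one to build on.

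**Conclusion.** The point holds in a limited form. Loss to follow-up is used as a censoring event without a date. Its missed-visit count is reached 9 months after the last attended visit by a participant who stops at or before month 15, and not at all by one who attends until month 18 or 21 and then stops. Unless permanent discontinuation is applied to silent dropouts and loss is dated back to the last contact, 3, 6 or 9 months without a visit can be counted as AMI-free, less what other contact covers.

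At an assumed 14.5% dropout, spread evenly and with no contact in the gap, credited time runs from about 0.7% to about 4.9% of person-time. The upper figure needs loss to be dated at the third missed visit. It is tempting to conclude that remote or low-access centres will look protected. The article gives no attendance by centre, so neither the direction nor the size of any bias between groups can be derived from it.

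**What to change.** In Primary outcome analysis, state that event-free participants are followed to the last date on which AMI status was ascertained by any route (clinic visit, telephone or electronic contact, or record check), however many visits were missed. Say explicitly that this covers participants missing only the month 21 visit, the month 24 visit, or both. Keep the rule of more than two missed visits only as a retention statistic. This also settles the case of someone who misses three scattered visits and returns.

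In the nested case–control component, build the risk set with the same censoring date, so that each control is known to be AMI-free at the case's index date.

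The cost is slightly less person-time, and the date of last contact with known AMI status must be recorded for every participant; the article does not say that it is. The change removes unobserved time from the denominator. It does not make dropout unrelated to AMI risk, so reporting retention by centre and ethnic group remains useful.

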### Variables and data collection

#### Baseline variables

At enrolment, participants undergo standardized assessments including questionnaires, physical examination, laboratory testing, cardiovascular imaging, and physiological monitoring (Table 1; Figure 2). These measurements are designed to capture both individual-level risk factors and population-level variation related to environmental and ethnic contexts. Sociodemographic variables include age, sex, ethnicity, residence type (urban or rural), education level, occupation, and household income. Clinical history captures physician-diagnosed hypertension, diabetes mellitus, dyslipidaemia, prior stroke or transient ischemic attack (TIA), and family history of coronary artery disease (CAD), together with current medication use. Lifestyle-related variables include smoking status, classified as never, former, or current smoking, alcohol consumption, dietary patterns, physical activity level, sleep quality, medication adherence, and psychological status, which may vary across environmental and sociocultural settings. Physiological measurements include systolic blood pressure, diastolic blood pressure, resting heart rate, body mass index, waist circumference, and body fat percentage (18). Laboratory biomarkers include inflammatory and cardiac stress markers, cardiac enzymes, and metabolic indicators reflecting glucose and lipid metabolism (Supplementary material) (13, 19, 20). Cardiac imaging includes transthoracic echocardiography and coronary computed tomography angiography (CCTA) where clinically indicated. Continuous 72-h electrocardiogram (ECG) and heart rate variability (HRV) monitoring are performed at baseline using a clinically validated wearable device (ref) (Supplementary material). Data are collected using standardized procedures and processed according to predefined quality-control criteria to ensure comparability across study sites.

**Table 1 tab1:** Schedule of assessments and data collection in the AMI cohort study.

Evaluation parameters	Baseline	Follow-up							
		3 m	6 m	9 m	12 m	15 m	18 m	21 m	24 m
Informed consent	x								
Inclusion criteria met	x								
Standardized assessment*	x								
Sociodemographic characteristics+	x								
Lifestyle factors++	x								
Clinical history†	x								
Anthropometry and physiological parameters‡	x	x	x	x	x	x	x	x	x
Fasting venous blood test**	x	x	x	x	x	x	x	x	x
72-h wearable electrocardiogram monitoring¶	x		x		x		x		x
Transthoracic echocardiography¶¶	x				x				x
CCTA (if there are clinical indications)***	x				x				x
Assessment tool¶¶¶									
Rose Angina Questionnaire	x	x	x	x	x	x	x	x	x
Canadian Cardiovascular Society Angina Classification	x	x	x	x	x	x	x	x	x
PHQ-9	x	x	x	x	x	x	x	x	x
GAD-7	x	x	x	x	x	x	x	x	x
PSS-10	x	x	x	x	x	x	x	x	x
PSQI	x	x	x	x	x	x	x	x	x
FFQ	x	x	x	x	x	x	x	x	x
IPAQ-SF	x	x	x	x	x	x	x	x	x
GMAS	x	x	x	x	x	x	x	x	x

Baseline assessment: The project will be carried out from 2025 to 2027 in Gansu Provincial People’s Hospital, Aksay County People’s Hospital, Linxia Prefecture People’s Hospital, Gannan Tibetan Autonomous Prefecture People’s Hospital, and Dingxi City People’s Hospital. High-risk cardiovascular patients of the Han, Hui, Tibetan, and Kazakh ethnic groups will be identified through cardiovascular outpatient clinics, community screening programs, and electronic medical record systems. Follow-Up: it will be conducted at 3, 6, 9, 12, 15, 18, 21, and 24 months after enrollment in the cohort, for a period of 2 years. *Standardized assessment: Demographics, lifestyle, psychology, diet, and medication adherence questionnaires. +Sociodemographic characteristics: Age, sex, ethnicity, residence type, education, occupation, and income. ++Lifestyle factors: Smoking, alcohol consumption, dietary habits, physical activity, and sleep quality. †Clinical history: Hypertension, diabetes, dyslipidemia, previous stroke or TIA, family history of coronary heart disease, and history of drug use. ‡Anthropometry and physiological parameters: Including height, weight, BMI, waist circumference, blood pressure and body fat percentage. **Fasting venous blood tests: High-sensitivity C-reactive protein (hs-CRP), high-sensitivity troponin I (hs-TnI), creatine kinase (CK), creatine kinase-MB (CK-MB), lactate dehydrogenase (LDH), aspartate aminotransferase (AST), soluble suppression of tumorigenicity 2 (sST2), N-terminal pro–B-type natriuretic peptide (NT-proBNP), lipoprotein-associated phospholipase A2 (Lp-PLA2), fasting glucose, insulin, hemoglobin A1c (HbA1c), and a full lipid panel (total cholesterol, low-density lipoprotein cholesterol(LDL-C), high-density lipoprotein cholesterol (HDL-C), and triglycerides. ¶72-h wearable electrocardiogram (ECG) monitoring: A validated clinical-grade device (Shanghai Yishi Technology Co., Ltd.) will be used to continuously conduct 72-h wearable ECG and heart rate variability (HRV) monitoring. The data will be transmitted in real-time to a secure cloud platform, and the NARON CardioAI system will be used for automatic analysis, waveform classification, and feature extractio. ¶¶Transthoracic echocardiography: Unless there are other clinical indications, an echocardiogram will be performed once a year to evaluate the left ventricular ejection fraction and the situation of abnormal wall motion. ***Coronary computed tomography angiography (CCTA): If there are clinical indications should be repeated every 12 months. Assessment Tools: Includes the Rose Angina Questionnaire, The Canadian Cardiovascular Society Angina Classification, The Patient Health Questionnaire-9 (PHQ-9), The Generalized Anxiety Disorder-7 (GAD-7), The Perceived Stress Scale - 10 (PSS-10), The Pittsburgh Sleep Quality Index (PSQI), The Semi-quantitative Food Frequency Questionnaire (FFQ), The International Physical Activity Questionnaire Short Form (IPAQ-SF), The General Medication Adherence Scale (GMAS).

**Figure 2 fig2:**
[figure not shown]
Schematic overview of the study design.

#### Follow-up assessments

Participants are followed every 3 months over 24 months using a standardized schedule (Table 1). This repeated-measures design allows assessment of temporal changes in risk indicators and their potential association with short-term cardiovascular events. At each visit, symptom status, interim medical events, medication use, and health-related behaviors are updated. Biomarkers are measured at regular intervals, and ECG monitoring is repeated every 6 months. Echocardiography is repeated annually, and CCTA is performed when clinically indicated. All suspected AMI events are adjudicated by an independent, blinded cardiology panel according to the Fourth Universal Definition of Myocardial Infarction (2018) (21).

#### Assessment tools

Standardized instruments are used to quantify lifestyle, psychological, and symptom-related variables (Supplementary Material 1). Angina symptoms are assessed using the Rose Angina Questionnaire and graded according to the Canadian Cardiovascular Society classification (22, 23). Psychological status is evaluated using the Patient Health Questionnaire-9 (PHQ-9) for depressive symptoms, the Generalized Anxiety Disorder-7 (GAD-7) scale for anxiety, and the Perceived Stress Scale-10 (PSS-10) for perceived stress (24–26). Sleep quality is assessed using the Pittsburgh Sleep Quality Index (PSQI) (27). Dietary intake is evaluated using a semi-quantitative food frequency questionnaire adapted to regional dietary patterns, and physical activity is assessed using the International Physical Activity Questionnaire Short Form (IPAQ-SF) (28, 29). Medication adherence is measured using the General Medication Adherence Scale (GMAS) (30).

#### Environmental and contextual data

Environmental variables, comprising monthly averaged meteorological parameters and air pollutant concentrations, were assigned to each patient according to their residential location and the date of hospital admission. Meteorological metrics, such as temperature, precipitation and relative humidity, were acquired from the ECMWF Reanalysis v5 (ERA5) product, which offers global coverage at a 0.25° × 0.25° gridded resolution (approximately 25 km at the equator) (3). For air pollution exposure assessment, concentrations of fine particulate matter (PM2.5 and PM10) (31), ozone (O3) (32), and nitrogen dioxide (NO₂) (33) were derived from the China High-Resolution and High-Quality Near-Surface Air Pollutants (CHAP) Dataset, which provides estimates at a high spatial resolution of 1 km. Elevation above sea level was also incorporated to account for its potential influence on AMI risk across different altitudes.

Healthcare access indicators include average travel time to the nearest secondary or tertiary hospital, hospital bed density, and physician density per 1,000 population (33). Information on socioeconomic factors, including city-level per capita income, employment patterns, occupational classifications, educational attainment, and housing conditions, will be systematically collected during scheduled follow-up visits and cross-referenced with official statistics from the Gansu Statistical Yearbook issued by the Gansu Provincial Bureau of Statistics, China.

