#### Longitudinal and short-term risk analysis

Repeated measurements of physiological and biomarker variables will be analyzed using linear mixed-effects models with random intercepts and random slopes when supported by the data. Time will be modeled as follow-up visit or continuous time since enrolment. Short-term risk will be evaluated using extended Cox models with time-varying covariates. Biomarker and physiological measurements will be updated at each follow-up visit and incorporated as time-dependent variables. For participants with incident AMI, measurements will be aligned relative to the event time. Predefined time windows preceding AMI will be constructed, and values within these windows will be analyzed. Within-individual changes will be defined as differences between consecutive measurements or relative to baseline values. Associations between time-updated variables and AMI risk will be estimated using time-varying Cox models.

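### Monthly weather and pollution exposures are dated by hospital admission, an event that entry to this cohort does not require and follow-up does not schedule

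*Protocol article*

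**What the plan says.** The dating rule appears once, under Environmental and contextual data. "Environmental variables, comprising monthly averaged meteorological parameters and air pollutant concentrations" are the variables concerned, and they "were assigned to each patient according to their residential location and the date of hospital admission". No other section gives a date for them.

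The rest of the article describes a prospective cohort whose members need not be admitted:

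- The notes to Table 1 say that high-risk patients "will be identified through cardiovascular outpatient clinics, community screening programs, and electronic medical record systems".
- Study population lists acute illness at enrolment among the exclusions.
- Primary outcome analysis sets the time scale: "Follow-up time will be calculated from enrolment to AMI, loss to follow-up, death, or end of study".

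The exposures are then used in three places. The prespecified covariates of the primary Cox model end with "diabetes status, lipid profile, and environmental exposures". Analysis of population heterogeneity uses environmental exposure as a subgroup and interaction variable. Risk prediction analysis lists it as a candidate predictor.

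On time-updating, the section on longitudinal and short-term risk says: "Biomarker and physiological measurements will be updated at each follow-up visit and incorporated as time-dependent variables". Environmental exposures are not named there.

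**The concern.** A covariate in a Cox model must have a value for every member of each risk set, fixed by a rule that does not look ahead to the outcome. Dating by admission meets neither condition in this cohort. A participant who stays out of hospital has no date. A participant with an AMI has one, and it is the date of the outcome. A participant admitted for another reason has a date set by a different health event after enrolment.

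Weather and pollutant levels vary by season, so the choice of month changes the value. If the month is chosen differently for those with and without the event, an association can appear where none exists. Environmental differences in short-term AMI risk are a stated aim of the study, and analysts following this rule would have to invent a date for most of the cohort, possibly after outcomes are known.

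**Working it through.** **1. Does the design give every participant an admission?** Recruitment is through clinics, community screening and records. Acute illness at entry is excluded. Time starts at enrolment, and the visits are three-monthly. None of these is a hospital admission, so the only one the design implies is for AMI.

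**2. How many have no AMI admission?** Inputs from Study population: 2,340 enrolled, 4% incidence over 24 months, about 80 events.

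- Full follow-up: 2,340 × 0.04 = 93.6 events. The stated 80 is reached with attrition of 1 − 80/93.6 = 14.5%. The article refers the calculation to a supplement that is not shown, so the 80 is not disputed here.
- At 80 events: 2,340 − 80 = 2,260 without an AMI (96.6%).
- At 93.6 events: 2,340 − 93.6 = 2,246.4 (96.0%).

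Some of these people will be admitted for other reasons. The documents do not say how many.

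**3. What if cases are dated at the event and everyone else at enrolment?** The article does not state this hybrid; it is one way an analyst might fill the gap. Assumptions not in the documents: no true effect, a monthly exposure of 40 + 20·cos(2π·month/12) units peaking in January, no spatial variation, and events spread evenly over 24 months.

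Twenty-four months are two full annual cycles, so the mean for cases is about 40 whatever the enrolment month. The mean for non-cases follows the enrolment calendar. Over April to September the cosine averages (0 − 0.5 − 0.866 − 1 − 0.866 − 0.5)/6 = −0.622; over the other six months it averages +0.622.

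| Enrolment | Mean, non-cases | Null odds ratio per 10 units | Rejection at 0.05 |
|---|---|---|---|
| Even over the year | 40 | 1.00 | 7.7% |
| 60/40 towards April–September | 40 + 20 × (−0.622 × 0.6 + 0.622 × 0.4) = 37.5 | 1.13 | 36% |
| All in April–September | 40 − 20 × 0.622 = 27.6 | 4.8 | 100% |

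(Logistic model, 300 simulations each.)

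A second set added spatial variation with SD 10 µg/m³ and used seasonal amplitudes of 10 and 20 (400 simulations each). Null odds ratios per 10 µg/m³ at the two amplitudes were:

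- April–September enrolment: 1.71 and 2.13
- March–November: 1.27 and 1.32
- October–March: 0.58 and 0.47
- All months equally: 1.00 and 1.00

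Rejection was 66% to 100% in the three uneven windows. An 18-month window from July to the December of the following year, also uneven, gave only 1.04 to 1.05, with 6% to 10% rejection.

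**4. What if admission means enrolment for everyone?** Under the same assumptions the odds ratio stays at about 1.0 and rejection is between 2% and 9% across the runs, so there is no such bias. The remaining question is what a single month measures. With spatial SD 10, sinusoidal season and even enrolment, the share of exposure variance that is persistent spatial difference is 100/(100 + amplitude²/2):

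- Amplitude 10: 100/150 = 0.67
- Amplitude 20: 100/300 = 0.33

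The rest is the season of recruitment. The two parts are equal when amplitude²/2 = 100, that is, at an amplitude of about 14.

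**The case against.** The best defence is that *admission* is a loose term for the enrolment visit. The article calls the study hospital-based, and the primary analysis relates baseline variables to time from enrolment. On that reading every participant has a date and it does not depend on the outcome. The past tense and the word for patient in the exposure section suggest phrasing carried over from a series of admitted cases, though that is inference. This reading is possible, and it removes the bias in step 3. But the text does not say it, and recruitment through clinics, screening and records does not fit it.

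A second defence is that exposure windows and lags belong in a fuller document. That is true of windows and lags. Here, however, the article states a rule, and the rule conflicts with its own recruitment and time origin.

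Some stronger inferences are tempting and are not supported:

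- *Only participants with an event are admitted.* Event-free members can be admitted too, and healthcare utilization is a secondary outcome.
- *The plan will produce the odds ratios in step 3.* They rest on a hybrid rule the article does not state, on assumed seasonality and enrolment windows, and on an unadjusted logistic model rather than the planned Cox model.
- *An enrolment-month exposure mostly measures the recruitment calendar.* At amplitude 10 two thirds of the variance is spatial.
- *The plan rules out time-updated environmental exposure.* The longitudinal section does not name it, but does not bar it.

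**Conclusion.** The stated date anchor does not fit the cohort. As written, it leaves the monthly weather and pollutant exposures without a valid common date for most of the roughly 96% of participants who have no AMI, or makes their timing depend on the outcome or another health event after enrolment. This conclusion comes from setting the sections side by side and does not rest on the simulations.

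The size of any resulting bias cannot be fixed from the article. Under hybrid dating and assumed seasonality it runs from none to severe and can go either way, depending on an enrolment calendar that is not stated. Under the enrolment reading there is no such bias. One month then represents exposure over up to 24 months and mixes recruitment season with lasting spatial difference, in proportions that depend on the local seasonal swing.

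A reader might infer that the whole environmental question is undermined. It is not: elevation and the healthcare access indicators need no admission date. The defect is confined to the dated monthly variables, but these enter the primary Cox model, the subgroup and interaction analyses, and the prediction models. The rule should be corrected before exposures are linked.

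**What to change.** Replace the admission date with an anchor that every participant has and that does not depend on the outcome:

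- **Time-varying use.** Assign monthly exposure by residence to every participant for each month of follow-up. Enter it as a time-varying covariate, evaluated for all members of the risk set at each event time. Adjust for calendar month or season: the Cox time scale is time since enrolment, so members of one risk set can be in different calendar months.
- **Baseline and subgroup use.** Take an average over a stated period anchored at enrolment instead of a single month. The preceding 12 months is one example; the choice of period is the sponsor's.
- **Nested case–control set.** The article plans biomarker analyses there, with controls drawn from the risk set. If environmental exposure is analysed there as well, date controls at the case's index date.

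The cost is protocol wording and some extra linkage code. The article already describes gridded data sources and monthly averages. No change to the sample size follows.
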